**Methods:**

Participating hospitals will collect data on all interventions performed during neonatal resuscitation over a period of 6 months. All hospitals providing perinatal care are eligible regardless of size and designated level of neonatal care. Every neonate requiring more interventions than basic drying and tactile stimulation during the first 30 min of life will be included. The targeted sample size is at least 4,000 neonates who receive interventions. After anonymization, the data is pooled in a common database and descriptive and statistical analysis is performed globally and in subgroups. Possible correlations will be investigated with phi coefficient and chi square testing.

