### Sample size

The targeted sample size was decided upon empirically. The rarest described intervention in the literature is the administration of epinephrine with a frequency of as low as 0.05% and we wanted to collect data on at least 20 infants receiving this intervention. Therefore, the calculated total number of births during the study period must equal or exceed 40,000. We expect at least 500 births per participating hospital during the study period, leading to a target of 80 participating hospitals. Assuming an intervention rate of 10%, this results in a sample size of 4,000 infants receiving interventions. As we wish to be able to strive to have meaningful comparisons between different levels of neonatal care and different healthcare systems, we are looking to include hospitals from 20 countries and if possible multiple hospitals of different neonatal care levels per country. Ideally, this would mean 4 hospitals per country, one per level of neonatal care. Participating hospitals will be recruited *via* direct contact, referrals by other hospitals and presentation of the study protocol at scientific congresses.

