### Data analysis

Data will be analysed globally and for specific, predefined subgroups for every independent variable (e.g., completed week of gestational age, mode of birth, designated level of neonatal care).

Descriptive analysis will be performed on all study variables including absolute numbers and percentages as well as median and range for numerical variables. For all observed interventions confidence intervals will be calculated on a confidence level of 0.95. Additionally, statistical analysis regarding possible correlations will be performed on all study variables using phi coefficient and chi square test of independence. Statistical analyses and graphical presentations will be performed using R (The R Foundation for Statistical Computing, Vienna, Austria).

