## Discussion

Supporting postnatal transition of neonates seems to be the most frequently performed medical intervention (3). National and international guidelines are regularly updated in order to recommend an evidence based approach towards neonatal life support (17). However, data on the frequency of different interventions is scarce, outdated and often localized and therefore not representative for different health care systems or levels of care.

This international and multi-centre survey will provide much needed data on the frequency with which interventions are currently applied in the DR. Furthermore, the survey will examine the influence of different factors on administered interventions. Thereby, it will not only provide up-to-date information for future guidelines but will also help to generate hypotheses for further research and designing future studies on DR-management.

Current guidelines recommend different interventions in order to support postnatal transition, with a special focus on respiratory support (17). As a result, non-invasive positive pressure ventilation is a relatively common intervention with described frequencies ranging from 4% to 12% of all neonates (14, 18). Other interventions like the administration of chest compressions or epinephrine are much rarer at described frequencies from 0.1% up to 0.3% (3, 18) and 0.05% to 0.3% (14, 19) respectively. However, little is known for other interventions.

Video recordings of neonatal resuscitation represent a possible solution to track performed interventions (20). By detailed analysis of video recordings, certain DR-interventions in preterm and term infants after c-section were previously described both for a single centre and as a comparison between different centres (21–23). However, this data is not representative for all infants.

The multi-centre and international approach of surveying current DR-management allows a comparison across centres of different sizes, levels of neonatal care and health care systems. The survey is easy to perform and not very time consuming, thus it is easy for hospitals to participate, ensuring large data sets. The prospectively planned stratification into different subgroups will provide detailed information for certain risk groups. Comparison of data from different countries will disclose variations that could be due differences in local guidelines, recommendations and practices.

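### Phi, the only association measure named, is not comparable across interventions with frequencies from 0.05% to 12%, and the asymptotic chi-square test is unreliable for adrenaline by country

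*Protocol article*

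**What the plan says.** The Data analysis section states that association analysis will be "performed on all study variables using phi coefficient and chi square test of independence". The abstract repeats this: "Possible correlations will be investigated with phi coefficient and chi square testing". Phi is the only measure of association named. No risk ratio, odds ratio or risk difference appears for any comparison.

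The Objectives ask for the impact of patient, structural and organisational factors on the interventions. Table 2 lists comparisons of each single intervention across mode of birth, care level, centre size, country and period of birth.

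The Sample size section is built on adrenaline, with a "frequency of as low as 0.05% and we wanted to collect data on at least 20 infants receiving this intervention", so that "the calculated total number of births during the study period must equal or exceed 40,000". It adds that "we are looking to include hospitals from 20 countries". The Discussion gives the spread of frequencies: 4% to 12% for non-invasive ventilation, 0.05% to 0.3% for adrenaline, and for compressions 0.1% to 0.3%.

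**The concern.** A measure of impact should mean the same thing for a rare intervention as for a common one. Phi does not, because its size and its largest attainable value depend on the margins of the table. A table of phi values would therefore partly order interventions by how common they are rather than by how strongly a factor acts on them. For a factor with more than two categories, phi also gives no direction.

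The test has a separate problem. Its large-sample approximation needs adequate expected counts, and the intervention that sized the study is expected about once per country. Country comparison is a stated strength of the survey, and significant results are the ones chosen for diagrams, so false country differences would be visible.

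**Working it through.** **The plan's own figures.** 20 / 0.0005 = 40,000 births; 40,000 / 500 = 80 hospitals; 40,000 × 0.10 = 4,000 treated infants. All three reproduce.

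**Phi for a given risk ratio.** Let p be the event frequency, q the share with the factor and RR the risk ratio. The article gives no caesarean share or other exposure share, so q = 0.30 is an assumption.

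- Risk without the factor: p0 = p / (1 − q + q·RR); risk with it: p1 = RR·p0
- phi = (p1 − p0) × √[q(1 − q) / (p(1 − p))]
- Ceiling, for p ≤ q: √[p(1 − q) / (q(1 − p))]

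At p = 0.0005 and RR 3: p0 = 0.0005 / 1.6 = 0.0003125 and p1 = 0.0009375. Then phi = 0.000625 × √(0.21 / 0.00049975) = 0.0128.

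At p = 0.10 and RR 3: p0 = 0.0625 and p1 = 0.1875. Then phi = 0.125 × √(0.21 / 0.09) = 0.191.

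| Event frequency | RR | phi | Ceiling |
|---|---|---|---|
| 0.05% (adrenaline, all births) | 3 | 0.013 | 0.034 |
| 0.5% (adrenaline, 20 of 4,000 treated) | 3 | 0.041 | 0.108 |
| 10% | 3 | 0.191 | 0.509 |
| 0.05% | 10 | 0.025 | 0.034 |
| 12% (upper figure for non-invasive ventilation) | 1.15 | 0.024 | 0.564 |

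The same threefold effect differs by 0.191 / 0.0128 ≈ 15 times. A tenfold effect on adrenaline and a 15% effect on ventilation give practically the same phi.

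**What the accompanying test does with a small phi.** In a 2×2 table, chi-square = N × phi². With N = 40,000, RR 3 for adrenaline gives 40,000 × 0.0128² ≈ 6.6, p ≈ 0.01. Complete association gives 40,000 × 0.0342² ≈ 47, p < 10⁻¹⁰. In two halves of 4,000, 16 against 4 events gives Pearson p = 0.007 and Fisher p = 0.012.

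**Expected events per stratum, equal strata.**

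- Adrenaline by country: 20 / 20 = 1 at 0.05%; 120 / 20 = 6 at 0.3%.
- Adrenaline by care level: 20 / 4 = 5 at 0.05%.
- Compressions by country: 40 / 20 = 2 at 0.1%; 120 / 20 = 6 at 0.3%.

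**Size of the chi-square test, adrenaline by country, 20 events, no true difference (simulated).**

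- Equal countries: rejection between 3.9% and 4.7% at nominal 5%, and about 1% at nominal 1%.
- Unequal countries, with assumed expected counts from 3.6 down to 0.14: 8.2% at nominal 5% and 3.4% at nominal 1%. Other assumed unequal layouts gave 2.5% to 3.8% at nominal 1%.
- Four equal care levels, for comparison: 4.7% at nominal 5%.

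At the upper adrenaline rate (120 events) the same unequal layout has six times these expected counts. Eleven of the 20 countries still fall below 5, the largest of them at 0.68 × 6 = 4.1.

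**The case against.** A reader might infer that strong associations for rare interventions will be reported as no correlation. The article does not support that. It sets no cut-off for phi, it pairs phi with a test that still flags strong two-group effects, and it promises to tabulate every result whatever its significance. Nor do sparse cells hide associations: in the unequal layouts the error is over-rejection. Low power by country comes from having only 20 events, and no choice of test repairs that.

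Two other readings also go too far. About one expected event per cell fits adrenaline by country at the lowest published rate; compressions have 2 to 6 per country. And phi is not always held near zero: among 4,000 treated infants the ceiling for adrenaline is 0.309 against a factor present in 5%, and about 0.71 for 20 adrenaline against 40 compression cases.

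It is also fair to say that percentages with 95% confidence intervals are planned, with frequencies by subgroup, so a reader could work out direction and ratios. A rule for small cells may stand in an analysis plan that is not shown, and the survey is observational and meant to generate hypotheses. This softens the harm. It does not make phi a usable measure of impact, and naming phi and chi-square for all study variables is a stated choice rather than an omitted detail.

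**Conclusion.** The point holds in two limited parts.

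1. Phi is the wrong measure for comparing effects across these interventions. The gap is about 15-fold for the same risk ratio between event frequencies of 0.05% and 10%. This rests on the assumed 30% exposure share; the exact figures move with that share, but the dependence on event frequency does not go away.

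2. At the planning minimum of 20 adrenaline events over 20 countries, the asymptotic test cannot be relied on. It is near nominal with equal countries and rejects about 8% at nominal 5%, and about 3% at nominal 1%, with unequal ones. The unequal sizes are assumed. They are plausible because hospitals of any size may join, although the protocol would ideally have four hospitals per country. The 20 events are a floor; at higher adrenaline rates the problem lessens.

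This is worth correcting before analysis. It does not threaten the descriptive frequencies, which are the survey's main product.

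**What to change.** In the Data analysis section and the abstract's Methods, replace phi with risk ratios (or odds ratios) and risk differences, each with a 95% confidence interval, for every factor. For factors with more than two categories, name a reference category. Where a stratum has no events, show the count and the risk difference, since the ratio is then zero or undefined.

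Keep the chi-square test where expected counts are adequate. State that exact or Monte Carlo p-values will be used where any expected count is below 5, notably for adrenaline by country.

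A trend term for ordered factors such as care level, centre size or gestational-age group is optional.

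The cost is a change of wording and slightly more analysis work. R, already named, has the functions, and no further data are needed.

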## Anticipated results

We are expecting that the targeted sample size of at least 4,000 neonates receiving interventions will be collected within 1 year of enrolling the first hospital. To reduce bias, we are looking to collect data on equal amounts of births for every level of neonatal care and to include a hospital of every level of neonatal care from every participating country.

The minimum of anticipated results of descriptive and statistical analysis is listed in Table 2. Further results of additional analysis might be added if the need emerges during the data analysis process. Selected results of descriptive analysis and significant statistical analysis will be presented in graphical form as diagrams. All results regardless of significance will be presented in tabular form, at the least as supplementary material of the planned publication.

**Table 2 T2:** List of anticipated results of descriptive and statistical analysis.

Descriptive analysis	Statistical analysis
Total intervention frequency (global and stratified into subgroups sorted by mode of birth, level of neonatal care, center size, country, weekly period of birth, daily period of birth)	Significant differences in total intervention frequency between the stratified subgroups (mode of birth, level of neonatal care, center size, country, weekly period of birth, daily period of birth)
Frequency of single supportive interventions (global and stratified into subgroups sorted by gestational age, mode of birth, level of neonatal care, center size, country, weekly period of birth, daily period of birth)	Significant differences in single supportive intervention frequency between the stratified subgroups (mode of birth, level of neonatal care, center size, country, weekly period of birth, daily period of birth)
Combined frequency of CPAP, non-invasive ventilation and invasive ventilation and frequency of primary intubation (without application of non-invasive respiratory support)	Significant differences in single supportive intervention frequency for neonates receiving interventions stratified by gestational age groups

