### Objectives

The overall aim of this survey is to estimate the frequency of various interventions applied to newborn infants in the DR and to investigate the impact of possible influencing factors such as centre size and location, level of neonatal care, working hours and weekly periods.

The main objectives of this study are:
1.To estimate the total frequency of interventions given to neonates in the DR in order to support neonatal transition and to compare this estimate with prior data.2.To estimate the frequency of single supportive interventions applied to neonates in the DR.3.To investigate the impact of the following patient-specific factors on supportive interventions:
a.gestational age (separated into different gestational age groups)b.mode of birth (c-section vs. vaginal delivery)4.To investigate the impact of the following structural factors on frequency of single interventions:
a.Designated level of neonatal care according to the definition of the American Academy of Pediatrics (AAP) (15)b.Centre size (defined by total number of newborn infants in 2021)c.Presence of trained neonatologists 24/7d.Centre location (defined by country)5.To investigate the impact of the following organisational factors on frequency of supportive interventions:
a.Weekly period of birth (Monday–Friday vs. weekend)b.Daily period of birth (00.00–08.00, 08.00–16.00, 16.00–00.00)Further objectives include:
6.To further elucidate the mode of respiratory support by analysing the combined frequency of the use of CPAP, non-invasive ventilation and invasive ventilation, and by analysing the frequency of primary intubation (without application of non-invasive respiratory support).7.To generate current data regarding surfactant administration in the DR by comparing the frequency of less-invasive surfactant administration versus application *via* endotracheal tube.8.To investigate the frequency of laryngeal mask use as an alternative airway management tool in the DR.9.To further elucidate the current practice regarding the route of drug administration by comparing the frequency of peripheral venous, umbilical venous and intra-osseous access in the DR.10.To evaluate certain indicators of adherence to ERC guidelines (e.g., oxygen supplementation in resuscitation of early pre-term infants).

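### Equal births per level of care help the between-level comparison but do not make the pooled global frequency representative or comparable with prior data

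*Protocol article*

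**What the plan says.** Under Anticipated results, the protocol article gives its recruitment aim and the reason for it: "To reduce bias, we are looking to collect data on equal amounts of births for every level of neonatal care". The Sample size section describes the layout: "we are looking to include hospitals from 20 countries", and "Ideally, this would mean 4 hospitals per country, one per level of neonatal care". Both are worded as aims, not as fixed quotas.

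Objective 1 is to "estimate the total frequency of interventions given to neonates in the DR in order to support neonatal transition" and "to compare this estimate with prior data". Objective 2 asks for the frequency of each single intervention. Objective 4a investigates the effect of level of care on single interventions.

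On analysis, the abstract says that "the data is pooled in a common database and descriptive and statistical analysis is performed globally and in subgroups", and the Data analysis section says: "Data will be analysed globally and for specific, predefined subgroups for every independent variable". Results are counts and percentages with 95% confidence intervals. Table 2 lists the total and single-intervention frequencies both globally and by subgroup, including level of care. No section mentions weighting or standardising the global figure. The limitations in the Discussion do not name the level mix.

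**The concern.** Equal allocation over strata is a good design for comparing strata. For an overall frequency it fixes a mix of strata that need not be the mix in the population of births. The article gives one reason, reduction of bias, without saying which estimate it applies to. A reader will naturally apply it to the headline figure, the total intervention frequency.

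At stake is the reading of objective 1. The article faults earlier data for not representing different health systems and levels of care. If intervention rates differ by level, the crude global figure depends on how many births were recruited at each level. A difference from earlier estimates could then be a difference in level mix, with no change in practice. More births do not cure this. The global single-intervention frequencies of objective 2 are affected in the same way.

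**Working it through.** **1. The plan's own figures (Sample size section).**
- Births: 20 / 0.0005 = 40,000.
- Hospitals: 40,000 / 500 = 80, which is also 20 countries × 4 levels.
- Infants with interventions: 40,000 × 0.10 = 4,000.

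All three reproduce. With equal births, each level has 40,000 / 4 = 10,000.

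**2. What the pooled percentage estimates.** With equal births it is Σ 0.25·p over the four level-specific rates p, that is, their simple average. The rate among all births is Σ w·p, where w is each level's share of births. The two agree only if rates do not differ by level, if births really are spread 25/25/25/25, or if differences happen to cancel.

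**3. Illustrative size.** The article gives neither p nor w, so both are assumed here. The rates stay within its quoted overall range (5% to 15% in the abstract, up to 16% in the Introduction). Levels run from lowest to highest. Each cell shows Σ w·p, then crude minus Σ w·p in percentage points.

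| Assumed rates (%) | Crude, equal births | Shares 35/30/20/15 | 50/25/15/10 | 60/25/10/5 | 10/20/30/40 |
|---|---|---|---|---|---|
| 8/9/11/12 | 10.0 | 9.5 (+0.5) | 9.1 (+0.9) | 8.75 (+1.25) | 10.7 (−0.7) |
| 6/8/12/14 | 10.0 | 9.0 (+1.0) | 8.2 (+1.8) | 7.5 (+2.5) | 11.4 (−1.4) |
| 5/8/12/16 | 10.25 | 8.95 (+1.3) | 7.9 (+2.35) | 7.0 (+3.25) | 12.1 (−1.85) |

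Example, first cell: 0.35×8 + 0.30×9 + 0.20×11 + 0.15×12 = 9.5. With a flat 10% at every level the difference is 0 for any shares.

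**4. Against the sampling error.**
- Ignoring clustering: 1.96 × √(0.10 × 0.90 / 40,000) = 0.29 points.
- With 500 births per hospital and an assumed intracluster correlation of 0.02: design effect 1 + 499 × 0.02 = 10.98; half-width 0.29 × √10.98 ≈ 0.97 points.

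Every non-zero difference in the table exceeds 0.29. Against 0.97, the differences of 0.5, 0.7 and 0.9 points fall inside the half-width and the others lie outside it.

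**5. Objective 2, one example.** The Discussion gives 0.05% to 0.3% for epinephrine. Assume 0.05/0.1/0.2/0.3% by level. The crude figure is 0.1625%. The weighted figure is 0.1325% (35/30/20/15), 0.09% (60/25/10/5) or 0.205% (10/20/30/40). The crude figure is then 23% too high, 81% too high or 21% too low in relative terms.

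**The case against.** The strongest reply is that the comparator matters. The realistic alternative to equal allocation is not a sample proportional to births. The Sample size section recruits through direct contact, referrals and congresses, and this may over-represent high-level centres. Take rates of 5/8/12/16% and an assumed unconstrained mix of 10/15/30/45. The crude figure is 0.5 + 1.2 + 3.6 + 7.2 = 12.5%, against 10.25% with equal births and 7.0% to 8.95% under the shares weighted to low levels. Equal allocation then lies closer to the population figure. This stands. A reader might infer that aiming for equal births adds bias to objective 1, or that the global figure will be too high. The article supports neither: it gives no rates or shares by level, and the sign reverses when births concentrate in high-level centres.

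Other points also stand:
- The target is an aim, so an exact 25/25/25/25 mix is not guaranteed.
- The bias meant may be that of the between-level comparison, where the allocation does help.
- Table 2 already plans frequencies by level, and these are not distorted by the allocation.
- Birth shares by level may not exist in 20 countries, the more so as the Survey sites section accepts regional equivalents of the level definition.
- The article describes prior data as old or mostly single-centre and does not give their level mix, so standardising may not make the two comparable.

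A full analysis plan might specify weighting. That would settle the estimator. It would not make equal allocation, in itself, a remedy for bias in the global frequency, and the article as written offers it as a bias-reducing step beside an unweighted global figure.

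**Conclusion.** The concern holds in a limited form. Equal births per level serve objective 4a. They do not make the global frequencies of objectives 1 and 2 representative. Those figures are the simple average of level-specific rates if the target is met, and a recruitment-mix average if it is not. If rates differ by level, which objective 4a sets out to investigate, comparison of the crude global figure with prior data is open to confounding by level mix.

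Size and direction cannot be derived from the article. Under the assumed rates and shares the difference is about 0.5 to 3 points and can take either sign. It is clearly larger than the half-width that ignores clustering (about 0.3 points). In the mildest scenarios it is no larger than a half-width of about 1 point, which itself rests on the assumed intracluster correlation of 0.02. Level-specific results are unaffected.

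**What to change.** Recruitment and data collection need not change: sites already report their level and their monthly births.

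- State that equal allocation serves the between-level comparison and does not remove bias from the global frequency.
- Make the level-specific frequencies already planned in Table 2 the basis for objective 1.
- Label the crude pooled figure as specific to the recruited sample, for total and single interventions alike.
- Add a directly standardised global figure, Σ w·p, with external birth shares by level where they exist. Where they do not, give a range over stated plausible level mixes.
- Compare with prior data only at a matching level or on the standardised range. Where the level mix of the prior data is unknown, say that the comparison is confounded by it.

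The cost is a little more analysis, weights that are approximate in some countries, and a less precise headline figure. In the scenarios tabulated above, the half-width of the standardised rate, 1.96 × √(Σ w²·p(1−p)/10,000), is 0.28 to 0.36 points before clustering, against 0.29 for the crude rate. The larger loss of precision comes from showing a range where the shares are uncertain.

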### Study variables

For every included neonate the following data are collected:
•Weekly period of birth (Mo–Fr/Weekend)•Time period of birth (8:00–16:00/16:00–0:00/0:00–8:00)•Completed week of gestation•Mode of birth (c-section/no c-section)•Application of the following items during neonatal resuscitation:
○Respiratory support:
◾ Initial inflations◾ CPAP◾ Non-invasive ventilation◾ Oxygen supplementation○Airway management:
◾ Suction*◾ Laryngeal mask◾ Endotracheal intubation + invasive ventilation○Drug application:
◾ Surfactant administration (*via* endotracheal tube)◾ Less-invasive Surfactant administration (LISA)◾ adrenaline◾ Caffeine○Vascular access
◾ Peripheral IV access*◾ Umbilical venous access◾ Intraosseous access○Chest compressions (if performed at least once)Marked items (*) will only be recorded if performed together with other interventions due to practicability aspects. Tactile stimulation is not recorded because while it is most likely applied to every neonate, the management varies widely between centres and there exists no consensus on the most effective stimulation method (16).

For detailed definitions of the variables see Table 1.

**Table 1 T1:** Definitions of study variables/data collection form items.

Study variable	Definition
Initial inflations	Positive pressure application using a facemask (at least ≥10 cm H_2_O over PEEP) over at least 2 s at least once before any other respiratory support
CPAP	Continuous positive pressure application (≥5 cm H_2_O) with sufficient device positioning and regardless of interface and pressure driver
Non-invasive ventilation	Intermittent positive pressure ventilation (iPPV) at least two times in a row regardless of interface and pressure driver; initial inflations excluded
Suction	Use of any suction device for airway clearance
Laryngeal mask	Insertion of laryngeal mask as airway device
Oxygen supplementation	Application of any additional oxygen, FiO_2_ > 0.21
Intubation + invasive ventilation	Ventilation *via* endotracheal tube (ETT); not to be ticked if intubation was used as mean for surfactant administration and the infant was extubated prior to the end of neonatal resuscitation
Surfactant *via* ETT	Surfactant administration *via* endotracheal tube, regardless of continuation of invasive ventilation after Surfactant administration
Less-invasive surfactant administration	Any other form of Surfactant administration less invasive than *via* endotracheal tube

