Peripheral i.v. access	Placement of peripheral IV access regardless of administration of fluids/drugs
Umbilical venous access	Placement of umbilical venous access regardless of administration of fluids/drugs
Intraosseous access	Placement of intraosseous access regardless of administration of fluids/drugs
Chest compressions	Administration of chest compressions at least for one cycle (three compressions) according to ERC guidelines
Adrenaline	Administration of adrenaline at least once, regardless of administration route

Additionally, the following baseline characteristics are collected for every survey site:
•Designated level of neonatal care according to the definition of the AAP (15)•Total births per year (historical data from 2021)•Number of admissions to the neonatal intensive care unit (either in-house or nearest available) per year (historical data from 2021)•Total number of infants born per month during the survey period•Total number of infants born per month *via* c-section during the survey period•Permanent availability of a trained neonatologist either in-house or on call

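### Total intervention frequency by weekly and daily period of birth is promised and tested, but births are not counted by period, so the rate per birth cannot be computed

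*Protocol article*

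**What the plan says.** Objective 5 is one of the main objectives: "To investigate the impact of the following organisational factors on frequency of supportive interventions". Its two factors are "Weekly period of birth (Monday–Friday vs. weekend") and "Daily period of birth (00.00–08.00, 08.00–16.00, 16.00–00.00").

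Table 2 (Anticipated results), described as the minimum to be reported, turns this into outputs. The descriptive cell of row 1 reads "Total intervention frequency (global and stratified into subgroups sorted by mode of birth, level of neonatal care, center size, country, weekly period of birth" and continues with daily period. The statistical cell of row 1 promises tests of differences in total frequency between the same strata. Row 2 does the same for single interventions, and its descriptive cell adds gestational age. The statistical cell of row 3 reads "Significant differences in single supportive intervention frequency for neonates receiving interventions stratified by gestational age groups".

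On data, Study variables introduces the individual record, which holds weekly and daily period, with "For every included neonate the following data are collected". Under the inclusion criteria a neonate is included only after receiving more than drying or stimulation. For births as a whole, sites give an annual total for 2021, "Total number of infants born per month during the survey period", and "Total number of infants born per month *via* c-section during the survey period".

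**The concern.** A frequency per birth needs treated infants in the numerator and all births in the denominator, both split by the factor of interest. For weekly and daily period only the numerator is split. The untreated row of the chi-square table does not exist for these two factors.

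At stake is a stated output of a main objective: whether infants born at the weekend or at night are treated more or less often. What the data do give is how treated infants are spread over the week and the day. That spread mixes the chance of being treated with the number of births in each period, and the plan has no means of separating the two. The limitations paragraph in the Discussion does not mention this.

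**Working it through.** **The plan's own figures.** Sample size: 20 / 0.0005 = 40,000 births; 40,000 / 500 = 80 hospitals; 40,000 × 0.10 = 4,000 treated infants. All three reproduce. They also show what the plan means by a frequency: the 10% and the 0.05% are both per birth.

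**Which strata have a birth denominator?**

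| Stratum in Table 2, row 1 | Birth count available |
|---|---|
| Global | Yes, sum of monthly totals |
| Mode of birth | Yes, monthly c-sections, and total minus c-sections |
| Level of care, centre size, country | Yes, these are site attributes, so site totals can be added up |
| Weekly period | None listed |
| Daily period | None listed |

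**Total frequency.** Let x_k be treated infants and n_k births in period k. The rate is t_k = x_k / n_k. The data give each x_k and the sum N of the n_k, but no single n_k, so t_k is not identified. Restricting to recorded infants does not help: all of them were treated, so the rate is x_k / x_k = 100% in each period and there is nothing to test.

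**Single interventions.** Let c_k be the share of treated infants in period k who received a given intervention. Every record holds both items, so c_k can be computed and a valid chi-square table built among recipients. The rate per birth is s_k = c_k × t_k. For two periods, s_1/s_2 = (c_1/c_2) × (t_1/t_2), and the last factor is unknown. Equal shares among recipients are thus compatible with unequal rates per birth, and the reverse.

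**How much the missing number matters (illustration only).** Take the planned 40,000 births and 4,000 recipients, and *assume* that 2/7 of recipients (1,143) are born at the weekend. The weekend share of births is also assumed, since the documents give none.

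| Assumed weekend share of births | Weekend rate | Monday–Friday rate |
|---|---|---|
| 20% | 1,143 / 8,000 = 14.3% | 2,857 / 32,000 = 8.9% |
| 25% | 1,143 / 10,000 = 11.4% | 2,857 / 30,000 = 9.5% |
| 2/7 | 10.0% | 10.0% |
| 30% | 1,143 / 12,000 = 9.5% | 2,857 / 28,000 = 10.2% |

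The same recipient data fit a higher, an equal or a lower weekend rate. This is a demonstration that the answer is undetermined, not an estimate of bias.

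**Gestational age, for comparison.** It is absent from both total-frequency cells, and its test in row 3 is explicitly limited to recipients, so the plan avoids the problem there. The descriptive cell of row 2, however, lists gestational age without that limit, and no births by gestational age are collected. The plan deals with this factor only in part.

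**The case against.** The best reply is that objective 5 speaks of the frequency of supportive interventions without saying per birth, and that each of about 4,000 records holds both period and interventions. Read as shares among recipients, row 2 is computable and the planned chi-square test applies. This stands. A reader might infer that objective 5 as a whole has no denominator and cannot be answered; the documents do not support that. What is missing is a *birth* denominator. The reply does not rescue row 1, where the share among recipients is 100% throughout. Nor does it settle row 2: the explicit limit in row 3 suggests that the rest of the statistical column is meant per birth, while the descriptive cell with gestational age points the other way.

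A reader might also infer that the survey will produce a false weekend effect of a known size. Dividing by calendar time (5/7 and 2/7 of births), with a true rate of 10% in both periods and an assumed 75% of births on Monday–Friday, would give 10.5% (3,000 / 28,571) against 8.75% (1,000 / 11,429). The arithmetic is right, but the plan nowhere proposes calendar denominators and the 75% is not in the documents. The figure shows only that this workaround would be unsafe.

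Two further replies carry some weight. The Data Collection Form is an attachment that is not shown; still, Study variables lists the site-level counts item by item, and none is by period. And the survey relies on being quick to complete, so extra counts have a price. That bears on which remedy to choose, not on whether one is needed.

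**Conclusion.** The point holds for row 1 of Table 2. Total intervention frequency by weekly and daily period, and the tests on it, cannot be produced from the data listed. For row 2, only the share among recipients can be compared by period, and described by gestational age, and the table should say so.

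The size of any resulting error is not estimable from the documents, because it depends wholly on the uncollected split of births over periods. The conclusion needs no assumption about when births cluster. It rests on two readings: that total frequency means per birth, as in the plan's own sample size, and that the site-level counts listed under Study variables are complete.

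The overall frequencies (objectives 1 and 2) and the total-frequency comparisons by mode of birth, level of care, centre size and country are unaffected. The planned numbers of births, hospitals and treated infants do not change.

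**What to change.** **Preferred.** Add to the monthly site report the number of births by Monday–Friday/weekend and by 8-hour period, preferably split by c-section, and use these as denominators for rows 1 and 2. The cost is 2 + 3 = 5 counts per site-month, or 10 when split by c-section. Over 80 sites and 6 months that is 5 × 480 = 2,400 or 10 × 480 = 4,800 counts. It assumes that sites can tally births by day and hour; the documents do not say so. If only some sites can, restrict the per-birth period analysis to those sites and do not mix it with shares among recipients from the others.

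**Otherwise, for all sites alike.** Delete weekly and daily period from both total-frequency cells of row 1, and label the row 2 results by period and by gestational age as being among neonates who received interventions. State in objective 5 that the comparison is conditional on having received an intervention. This costs only wording, but gives up the question of whether the chance of being treated differs by time of birth. The limitations should then say so.

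Under the second option, gestational age is settled as well. Under the first, the descriptive cell of row 2 still needs that label for gestational age, unless births by gestational age are counted too.
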